## Abstract

**Background:**

The overarching objective of the study is to obtain a comprehensive understanding of the salient factors predicting changes in physical activity (PA) during adolescents’ transition into emerging adulthood. Using the Multi-Process Action Control model as our guiding framework, we will examine how implicit and explicit psychological processes along with regulatory practices impact PA change during this major life transition. Additionally, we will use a real-time data capture method called Ecological Momentary Assessment to further investigate how environmental and contextual factors, and momentary psychosocial influences effect PA patterns across this dynamic life stage.

**Methods:**

The ADAPT study is a 4-year project comprised of two interrelated studies. Study I is a large prospective cohort study that will invite all grade 11 students across one large school board (a total of seven secondary schools) to participate by completing an online questionnaire. Using a cluster randomization approach, a subset of students from each school will be invited to participate in Study II, whereby participants will wear an accelerometer and complete Ecological Momentary Assessments 5 times a day over a 7-day study period. For both studies, following baseline assessments, there will be three annual follow-up assessments approximately 12 months apart.

**Discussion:**

The current study represents one of the largest longitudinal cohort studies examining PA and its determinants and associated consequences among adolescents transitioning out of high school into emerging adulthood. Findings from this study will provide a much more in-depth understanding of how and why changes in PA behaviour occur across this first major life transition.

## Background

Physical inactivity has become a major public health concern [1–3]. Indeed it is well established that the lack of physical activity (PA) engagement is associated with increased risk of several chronic diseases, directly contributing to high health care costs [4–6]. However, it also carries significant indirect and social costs such as time off work, lost productively, and psychosocial problems (e.g., low self-esteem, low sense of competence, delinquency) [7–10]. In terms of total estimated energy expenditure, trends suggest that PA peaks during the adolescent period, with significant declines in participation thereafter [10, 11]. In Particular, the transition from adolescence into emerging adulthood has been identified as a specific point for which steep declines in PA occur [12–20].

The transition into emerging adulthood is often considered the first major life transition [21–24], representing a period for which individuals acquire greater autonomy and some characteristics of adulthood without fully reaching the milestones that socially define contemporary adulthood [24]. The notable life event within this transition period is high school graduation. The specific transition out of high school is found to be associated with major changes in lifestyle behaviours, including PA [12]. Specifically, the literature has been very consistent in showing that PA behaviours are higher when individuals are in high school compared to the year following high school graduation [12–19]. There are a number of notable limitations that exist within the aforementioned body of evidence and require further investigation. First, few studies have followed participants from high school, instead relying on participants to retrospectively report PA during their high school years despite having already graduated. Second, few studies have used objective physical activity measures such as accelerometers to follow individuals over time. Third, in comparison to behavioural studies examining PA declines, few studies have investigated how changes in social cognitive factors relate to the changes in PA behaviours. Finally, little is known about how changes in social, environmental, and contextual factors may be influencing behaviour change during this transition.

In order to inform and develop effective long-term population-level interventions to target PA decline during the transition from adolescence to emerging adulthood, a better understanding of the underlying socio-environmental and psychological processes related to changes in PA behaviour is essential. Existing research that has investigated how psychosocial factors relate to PA behaviours around this life stage has been primarily based on social cognitive theories such as Theory of Planned Behaviour [25] and Social Cognitive Theory [26]. These theories suggest that behaviour is largely a function of an evaluation of expected behavioural outcomes and the confidence to perform it, manifesting through the conscious formation of an intention to enact the behavior [25–29]. Accordingly, while primacy has been given to these antecedent factors, few studies have focused on the non-conscious, social, and environmental influences. Moreover, little consideration has been given to within-subject changes (i.e., variability) and the influences of momentary (day-to-day, hour-to-hour) fluctuations in PA-related cognitions. As a result, despite the transition into emerging adulthood being highly dynamic, we have little knowledge about how changing contextual environments, variable affective or motivational states, and shifting opportunities may be influencing changes in PA during this life stage.

Action process-based models are becoming increasingly popular, particularly the application of integrative approaches to include post-intentional psychological constructs to bridge the intention-behaviour gap [30–34]. The Multi-Process Action Control (M-PAC) framework [35] represents one recent example. Described as a harmonized model based on well-established antecedents of PA behaviour and the integration of regulatory constructs to better explain PA behaviours. What makes M-PAC particularly unique is that it also allows for less conscious influences such as habit and identity impacting PA behaviours at the maintenance phase. M-PAC positions PA to be processes-based with PA being influenced by three central constructs: reflective processes to denote the consciously deliberated expected consequences of performing PA and the act of behavioral performance (i.e., intention formation); regulatory processes that include behaviours or cognitions that people enact to translate their intentions into physical activity behavior (i.e., self-regulated behavioural action); and reflexive processes that represent impulsive or less reasoned constructs that influence action control most often through learned associations and are triggered through particular circumstances and stimuli (i.e., habits and identity). To date, however, few studies have attempted to examine the M-PAC model in its totality.

It is also important to acknowledge that associations between psychosocial factors and PA have generally been examined at the between-person level only. That is, most studies have assessed an aggregated form of motivation and behaviour (i.e., a general rating of what you think about how active you would like to be over a specified period of time, and how much PA you engaged in over that period) [36] . The primary limitation of this approach is that an aggregated or gestalt perception about a behaviour assumes and considers motivation or perceptions to be stable across time. Emerging evidence based on several diary-based studies suggest that young people’s cognitions, and subsequent behaviours tend to vary over the course of a day [36–39]. Understanding the impact of within-person variations as it relates to how an individual may be thinking and its influence of how they behave is important, particularly if we can understand momentary cognitions using an existing theoretical framework such as the M-PAC model. The current protocol paper will describe the proposed procedures and methodology for a study aimed at addressing some of these aforementioned limitations – the ADAPT study: Application of integrateD Approaches to understanding Physical activity during the Transition to emerging adulthood.

## Methods

### Study design

The ADAPT study is comprised of two interrelated studies. Study I begins as a school-based study, using a prospective cohort design to follow a group of individuals during the broader transition from adolescence to emerging adulthood. Specifically, it is questionnaire-based, aiming to recruit a robust sample of as many of the grade 11 students across one large school board (a total of seven secondary schools), serving a socially and economically diverse metropolitan centre located in Southern Ontario. A subset of Study I participants will be invited to participated in Study II. Using a cluster randomization approach, two or three classes from each of the seven schools will be selected and subsequently invited to participate in Study II**.** This related study will involve more intensive social cognitive and PA assessments using ecological momentary assessments or EMA. For both studies, following baseline assessments, there will be three annual follow-up assessments approximately 12 months apart – the idea being to follow participants as they complete their final years at high school and first 2 years following graduation.

### Recruitment Strategy & Study Protocol

#### STUDY I

Baseline assessments will take place in classes, and all grade 11 students at each of the participating schools (ages 14–17) will be asked to voluntarily participate in this study. On average, the school board estimates that there are 300 grade 11 students in each school, and we expect that 80% will agree to complete the baseline questionnaire assessment. Having established a strong partnership with the school board, each of the seven secondary schools have agreed to participate in the larger study, and each with a nuanced and individualized recruitment strategy. Across each school, letters of information and consent forms will be sent out to students and parents approximately 1 week in advance of the school data collection date. The data collection date will fall within a five-week data collection period, mutually agreed upon between the school and study team. Data collection will occur during the first period of classes at each school, whereby all students will be invited to use the first 20 min of class to complete the online questionnaire. Each teacher will be informed in advance by school administrators and will provide students with the link to the questionnaire. Research assistants will be on site for all data collection dates, attending each classroom to provide further background to the study, answer any student questions, and/or to troubleshoot any potential problems with the online questionnaire. Participation is voluntary for students, but each student will be provided a $10 gift card if they choose to participate.

The vast majority of students will still be in high school during the initial follow-up (approximately 12-months later), thus the data collection period will again take place at the secondary schools. However, given that the final two data collection periods will take place following high school graduation, attempts will be made to re-contact participants via e-mail or other contact information provided to the study team. During each follow-up period, participants will be required to complete an online questionnaire, receiving a $10 gift card for each time they participate.

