#### Self-reported physical activity

The International Physical Activity Questionnaire – Short Form (IPAQ-SF) will be used to measure PA [40, 41]. Specifically, participants will be asked to respond to 3 items and indicate, during the last 7 days, on how many days they did 1) vigorous physical activities, 2) moderate physical activities, and 3) walked for at least 10 min at a time. If they indicate that they participated in an activity for one or more days, then they will be asked to indicate how much time (hours and/or minutes) they usually spent on one of those days participating in that activity.

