#### Physical activity cognitions

The physical activity cognitions measures included are largely based on the M-PAC model [35]. Below are the specific measures included:

*Affective and Instrumental Attitudes* will be measured using 6 items and presented on a 7-point bipolar scale [42]. Each item will be prefaced with the stem “*Over the next 4 weeks, being physically active, for me, will be*”. The affective component will be captured by three items: unpleasant-pleasant, boring-fun and unenjoyable-enjoyable. The instrumental component will be captured by the three items: harmful-beneficial, bad-good and useless-useful.

*Behavioural Intention* for engaging in PA will be measured using a single item measure commonly used in the PA domain [43]. Participants will be asked to rate the extent to which the following statement is likely: “*I intend to do at least 150 minutes per week of moderate-to-vigorous physical activity*”. Response options will range from 1 (*extremely unlikely) to* 7 (*extremely likely)*.

*Task and Barrier self-efficacy* will be measured by adhering to recommendations from Bandura (2006) for assessing self-efficacy [44]. That is, each item will be prefaced with the stem “*How confident are you in your ability to* …” with responses ranging from 0 (*Not Confident*) to 10 (*Completely Confident*). For task self-efficacy, participants will be asked to rate their confidence to perform 7 items relating to physical activity behaviour such as *“to engage in PA*”, “*to engage in sports*”, “*to jump, hop, and skip*” and “*to balance*”. For barrier self-efficacy, participants will be asked to rate their confidence in being physically active if “*the weather was very bad*”, their “*schedule conflicted with [their] activity session*” and “*even if [they] felt overwhelmed with things to do*”.

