### Data analysis

For Study I, Structural equation modeling (SEM) and mixed effects modeling (MEM) will be used to address the primary research objectives of the current study. SEM will be used to test the M-PAC framework, modeling and identifying key influences related to PA pre-transition, and to examine the changes in latent (i.e. unobserved constructs) and observed variables through the transition into emerging adulthood. MEM or growth curve modeling will be used to examine the influences of individual factors on PA behaviours accounting for individual students nested within their classrooms and nested within schools. Our models will include indicators of SES and social cognitive factors (i.e., mediators), being entered as time-varying independent variables, while other socio-demographic factors (moderators) will be entered in our models as time-invariant independent variables.

For Study II we will use *time-varying effects modeling* (TVEM) to investigate the associations between momentary cognitions and subsequent PA [61]. TVEM models examine changes in the associations between intensively sampled environmental-contextual or momentary social cognitive factors as it relates to PA behaviours over time. This method can accommodate the unequal spacing of observations and unequal assessments across participants, typical of studies using EMA. Modeling time effects with intensive longitudinal data captures complex patterns of variation, and generally produces confidence regions rather than the *p*-values associated with hypothesis testing.

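### At the two in-school waves each school's students recall nearly the same week, and the nesting stated for Study I does not separate that week's effect from mean change in physical activity

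*Protocol article*

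**What the plan says.** All references are to the protocol article.

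- **Collection date** (Methods, STUDY I): "The data collection date will fall within a five-week data collection period, mutually agreed upon between the school and study team". The whole grade answers in one class period: "Data collection will occur during the first period of classes at each school, whereby all students will be invited".
- **Outcome window** (Self-reported physical activity): the short-form IPAQ asks, "during the last 7 days, on how many days they did" each type of activity.
- **First follow-up** (STUDY I): most students are still at school, "thus the data collection period will again take place at the secondary schools". The Discussion adds that this wave uses the first part of a class, as at baseline.
- **Last two waves** (STUDY I): these follow graduation, and "attempts will be made to re-contact participants via e-mail or other contact information provided to the study team". No school date applies.
- **Spacing** (Study design): the three follow-ups are annual, about a year apart.
- **Model** (Data analysis): mixed-effects or growth curve modelling, "accounting for individual students nested within their classrooms and nested within schools". The time-varying terms named are socioeconomic indicators and social cognitive factors. Survey date, season and a school-by-wave term are not named. The same section makes change in observed variables across the transition an aim of the structural equation models.

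**The concern.** One date per school and a 7-day recall give every student at a school almost the same reporting week. Pre-graduation activity is then observed through about 14 school-weeks (7 schools x 2 waves), however many students answer. Weather, a test period or a break in that week can move a whole school together. The article's own barrier self-efficacy items (Physical activity cognitions) include being active if "the weather was very bad" and when schedules conflict.

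A school or classroom intercept that is constant over waves cancels out of a within-person change. A shock to one school in one wave does not cancel. If the model has no term for it, the shock goes into the residual and is treated as independent between students. The reported standard error of mean change between the two in-school waves, or of a post- versus pre-graduation contrast, is then too small, and ordinary week-to-week variation could be read as change over the transition.

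**Working it through.** The article gives no variance, intraclass correlation or power figure for Study I, so there is nothing of its own to reproduce beyond the expected sample.

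**Inputs from the article.** Schools S = 7; students per school m = 300 x 0.80 = 240; total 7 x 240 = 1,680; shared collection dates at waves 1 and 2 only.

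**Assumptions.** Total variance is 1 per occasion. Half of it (0.5) is within-person. A share s is common to one school on one occasion, with s = 0.001, 0.005 or 0.01. The model fits only wave-constant person, classroom and school effects.

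**Wave 1 to 2 mean change**

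- Reported variance: 2 x 0.5/1,680.
- True variance: 2s/7 + 2 x 0.5/1,680.
- SE ratio = sqrt[1 + (2s/7)/(1/1,680)] = sqrt(1 + 480s).

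**Mean of waves 3-4 minus mean of waves 1-2** (week effect in waves 1-2 only, full retention)

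- Reported variance: 0.5/1,680.
- Added variance: 2s/28 = s/14.
- SE ratio = sqrt[1 + (s/14)/(0.5/1,680)] = sqrt(1 + 240s).

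Rejection rate of a nominal 5% test = 2 x [1 - Phi(1.96/ratio)].

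| s | Wave 1-2 ratio | Rejects | Post-minus-pre ratio | Rejects |
|---|---|---|---|---|
| 0 | 1.00 | 5% | 1.00 | 5% |
| 0.001 | 1.22 | 11% | 1.11 | 8% |
| 0.005 | 1.84 | 29% | 1.48 | 19% |
| 0.01 | 2.41 | 42% | 1.84 | 29% |

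**Attrition.** If a fraction r of students is retained at all waves, the second ratio becomes sqrt(1 + 240rs). At s = 0.01 this is sqrt(2.44) = 1.56 for r = 0.6 (rejects 21%) and sqrt(1.96) = 1.40 for r = 0.4 (16%).

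**Within-person share.** Taking the within-person correlation as 0.3 to 0.7 instead of 0.5, the wave 1-2 ratio at s = 0.01 runs from 2.10 to 2.99.

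**Simulation check** (4,000 runs, within-person correlation 0.5). With wave-constant levels only, the wave 1-2 test rejected in 4.8% of runs at s = 0, 28.8% at 0.005 and 42.0% at 0.01. A t-test on the 7 school mean changes (6 df) stayed between 4.8% and 5.4% for s from 0 to 0.02.

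**Calendar-date bias, if dates do shift.** Assume an annual cycle of amplitude A = 10% to 20% of mean activity, at its steepest point, where the slope is 2 x pi x A/52 per week: 1.2% to 2.4%.

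- School dates independent and uniform over five weeks at each wave: a date has variance (25 - 1)/12 = 2, so one school's shift has SD sqrt(4) = 2 weeks. The mean over 7 schools has SD 2/sqrt(7) = 0.76 week, which is 0.9% to 1.8% of mean activity and zero on average.
- All seven schools shift four weeks in the same direction: 2A x sin(pi x 4/52) = 4.8% to 9.6%.

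**The case against.** The strongest reply is that the Data analysis section never lists the random effects. Growth curve modelling does not rule out school-level random slopes, and an article commonly leaves such detail to the full protocol or analysis plan. This stands as a limit. A reader might infer that the model is confined to wave-constant intercepts, but the text does not say so. What can be said is that the nesting it does state, read naturally, does not match the shared recall week that its own collection procedure creates. A school slope would absorb part of the effect, though a linear slope does not represent a shock in a single wave.

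A reader might also infer that school dates move every year. The documents do not support this. Only two of the four waves are collected in schools, the five-week window appears in the baseline description, and nothing says that a school's date will drift. The rule that waves are about a year apart roughly holds season constant. A bias of 5% to 10% therefore needs every school to move together by the maximum and is a worst case. The standard-error problem does not depend on drift, because a matched date can still fall in a different kind of week.

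A third reply is that the main target is which factors predict change, not the mean change itself. This stands in part. Coefficients of student-level predictors that vary within a school and wave are much less affected, so it would be wrong to conclude that the Study I findings as a whole are undermined. Mean change through the transition is still a stated aim.

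Finally, weather and breaks are largely shared across one board in one city. A school-by-wave term cannot remove an effect common to all schools in a wave. This stands and limits what the fix can do.

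**Conclusion.** The point holds in a limited form. At baseline and the first follow-up, a school's students share nearly one recall week, and the stated nesting does not, on its natural reading, separate that week from change in physical activity. That the first follow-up again uses one date per school is inferred from its being run in class, as at baseline.

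With about 240 students per school and only 7 schools, a small school-week variance is enough to matter for mean change: the SE ratio is already 1.22 for the wave 1-2 change at a 0.1% share. The share itself is assumed, since the article gives none, and at zero there is no problem. Inflation is smaller for contrasts that include the post-graduation waves, and smaller again with attrition. Calendar-date bias is conditional on dates shifting and is probably about 1% to 2% of mean activity (SD) if schools shift independently.

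This is worth correcting for mean-change estimates. It is no reason to doubt the within-school, within-wave associations.

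**What to change.** 1. For mean-change estimates in Study I, add a school-by-wave effect for the two in-school waves, with small-sample inference for 7 schools (for example t on 6 df for the wave 1-2 change).
2. Take the completion date from the online questionnaire, use it as the time variable in place of the nominal wave, and add a seasonal term.
3. Where feasible, keep each school's follow-up close to its baseline calendar week, and send post-graduation invitations in the same period.
4. State as a limitation that week effects common to all schools remain confounded with wave.

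**Cost.** One variance component, one date term and a scheduling sentence, with no data beyond the questionnaire's time stamp. Intervals for mean change become wider, and schools lose a little freedom over dates. The seasonal term may be imprecise, because the in-school waves supply at most 14 distinct dates (7 x 2). Item 3 has to be settled before the follow-up dates are agreed; the analysis items can be added later.
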